### Statistical analysis

The calculation of the sample size is based on the primary outcome (accuracy, visual n-back task of the TAP) for the intra-individual comparison within the different groups using a crossover design. The power analysis was done using Stata based on a paired means test. A noninferiority margin of 4% in working memory (n-back task) is regarded as clinically irrelevant. This margin is based on a study with healthy adults presenting a standard deviation of 4% in the accuracy condition of the n-back task [46]. Hence, a performance change in the n-back task of 4% or less would support our noninferiority hypothesis. According to Zimmermann and Fimm (2009), the test-retest reliability of the n-back task is 0.67 [37]. The correlation between two periods will be lower. Therefore, a correlation of 0.5 was assumed for this sample size calculation. Based on reported standard deviations in a n-back task in patients with PKU ranging from 5% to 8% (off-diet: SD = 7.6; on-diet: SD = 5.7 [27]), a standard deviation of 8% is expected (assuming that patients are off-diet during the 4 weeks Phe treatment). Based on these assumptions, the PICO Study will be able to detect noninferiority at a margin of 4%, a power of 80%, and a one-sided alpha level of 0.05, with a sample size of 26 patients. From earlier studies, including patients with PKU in Bern [47], patients with PKU are known to be highly motivated. Still, we might need to compensate for possible dropouts, which are suggested to fall between approximately 18% and 30% in other studies including patients with PKU [24, 28]; therefore, the goal has been set to 30 patients. Additionally, the effect size that would be detectable at different sample sizes and correlations for the comparison of the healthy control group and the experimental group (assuming the same number of controls and patients) was assessed. With a sample size of twice 26 participants and a power of 80%, an effect size of 0.79 could be detected at a two-sided alpha level of 0.05. To match the number of patients, the goal has been set to 30 controls.

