Data will be analyzed according to the intention-to-treat (ITT) principle whereby all randomized participants will be analyzed in the randomized group regardless of any protocol violations. Moreover, data will be analyzed in the per-protocol patient set, excluding patients who did not receive the randomized treatment schedule, patients who did not comply with the intervention (i.e., unable to follow all four time points, unable to adhere to the treatment arms), or patients who violated major eligibility criteria (i.e., onset of a pregnancy, onset of a concomitant disease status that could affect primary or secondary outcome).

The primary analysis will be performed in the randomized patient group. As recommended by the CONSORT statement for noninferiority trials [48], the analysis of the primary outcome will be based on the ITT as well as per-protocol patient set. Raw data of the n-back task will be transformed into standardized values using age matched normative data from the test manual. Normality of data will be assessed via graphical representation of data. Linear mixed effects models will be used to calculate the lower one-sided 95% confidence limit of the primary outcome. If the lower limit lies above the noninferiority margin of 4% in both analysis sets, noninferiority will be claimed. The mixed effects model will contain the baseline measurements, the 4 weeks measurements, and an indicator for the treatment and period as fixed effects, and a random effect for participants. All primary and secondary continuous endpoints will be analyzed via this approach. Secondary outcomes will primarily be analyzed in the ITT patient set. Secondary outcomes will additionally be evaluated in the per-protocol patient set. Furthermore, processed neuroimaging data will be compared in a cross-sectional and longitudinal manner. Due to the expected heterogeneity of the patient sample, comparisons will be focused on intra-individual changes of cerebral metabolism and functional integrity (comparison Phe vs placebo). Differences between groups will be investigated by linear mixed models, as described above. For the comparison of baseline values between patients and controls, regular linear regression models adjusted for potential confounders will be used.

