One interim analysis is planned for the reassessment of the sample size. Currently no reliable data are available on the correlation between the baseline and 4-weeks measurement and between the two different treatment periods for the n-back test. Therefore, the sample size will be re-assessed after 50% of patients to assure sufficient power. The re-assessment of the sample size will only be based on the observed standard deviations and correlations between baseline and follow-up values and between treatment periods. Observed changes within and between treatment periods will not be displayed, nor will the noninferiority margin be modified. No formal testing will take place; therefore, the alpha-level does not require adjustment.

Simple descriptive statistics will be used for evaluation of questionnaires on adverse events and mood. No formal statistical testing will be performed.

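### The 80% power at 26 patients belongs to a paired comparison without baselines, not to the primary mixed model, whose power depends on how baselines enter and on a correlation that the protocol does not give

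*Protocol article*

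**What the plan says.** All the relevant text is in the Protocol article under Statistical analysis.

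- **Sample size.** "The power analysis was done using Stata based on a paired means test". The inputs are a margin of 4%, an SD given as "a standard deviation of 8% is expected", one-sided alpha 0.05 and power 80%, leading to 26 patients and a recruitment goal of 30.
- **Correlation.** After stating that "the test-retest reliability of the n-back task is 0.67", the text continues: "The correlation between two periods will be lower. Therefore, a correlation of 0.5 was assumed for this sample size calculation". The 0.5 is thus tied to the two treatment periods.
- **Primary model.** "The mixed effects model will contain the baseline measurements, the 4 weeks measurements, and an indicator for the treatment and period as fixed effects", plus a participant random effect. The sentence lists baseline and 4-week values side by side among the fixed effects and does not name the response. The same approach is to serve all primary and secondary continuous endpoints.
- **Interim.** "Currently no reliable data are available on the correlation between the baseline and 4-weeks measurement and between the two different treatment periods". The sample size will be re-assessed at 50% of patients from observed SDs and from both kinds of correlation. The variance formula is not named.

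**The concern.** The paired calculation has no place for T1 and T3, whereas the model that yields the decisive confidence limit contains them. Adding a baseline covariate is usually expected to help, or at worst do nothing. In a crossover with a participant random effect that need not be so.

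Phe versus placebo is a within-patient contrast. A single baseline slope is fitted jointly to two relations. Between patients, high baseline scorers are high follow-up scorers. Within a patient, a higher baseline in one period may say little about that period's 4-week score. If the within-patient relation is weak, the pooled slope over-corrects the contrast and brings in the noise of T1 minus T3. At stake is the precision of the primary noninferiority limit, and whether the stated 80% can be relied on for it.

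**Working it through.** **Inputs.** From the protocol: SD 8, between-period correlation 0.5, margin 4, one-sided alpha 0.05, n = 26. Assumed: true difference 0; 26 completers; between-period correlation 0.5 for every pair of visits from different periods; baseline-to-4-week correlation within a period, r, from 0.4 to 0.67. Units are the percentage points of the sample size calculation.

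**Step 1: the plan's figure.** SD of the paired difference = 8 × √(2 × (1 − 0.5)) = 8. SE = 8/√26 = 1.57. The noncentral t gives power 79.8% at n = 26 (81.2% at 27; the normal approximation gives 81.7% at 26). The stated 26 reproduces, without any baseline term.

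**Step 2: one baseline slope, r = 0.5.** Split each patient's data into scaled sums and differences over the two periods (each divided by √2).

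- Sums: the variance of both follow-up and baseline is 64 × 1.5 = 96, and their covariance is 64 × (0.5 + 0.5) = 64. Between-patient slope = 64/96 = 0.67.
- Differences: both variances are 64 × 0.5 = 32, and the covariance is 64 × (0.5 − 0.5) = 0. Within-patient slope = 0.
- The likelihood weights the two slopes by information. At slope b the residual variances are 96 − 128b + 96b² and 32 + 32b². The self-consistent solution is b = 0.44: residual variances 58.2 and 38.3, weights 96/58.2 = 1.65 and 32/38.3 = 0.84, and (1.65 × 0.67 + 0.84 × 0)/(1.65 + 0.84) = 0.44.
- SD of the adjusted Phe-placebo difference = √(64 × (1 + 0.442²)) = 8.75. SE = 8.75/√26 = 1.72. Power (24 df) = 73.2%.

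**Step 3: one baseline slope, r = 0.67.** The between-patient slope is 64 × 1.17/96 = 0.78 and the within-patient slope is 64 × 0.17/32 = 0.34; the pooled slope is 0.65. The two unscaled period differences have covariance 64 × (2 × 0.67 − 2 × 0.5) = 21.76. Adjusted SD = √(64 + 0.651² × 64 − 2 × 0.651 × 21.76) = 7.92. Power = 80.4%.

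**Step 4: simulation.** Random-intercept REML fits at n = 26, two separate runs (10,000 / 4,000 trials per cell), power in %:

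| r | no baseline | one slope | mean + deviation |
|---|---|---|---|
| 0.40 | 79.6 / 78.5 | 73.0 / 71.9 | 79.1 / 78.3 |
| 0.50 | 80.0 / 79.0 | 73.7 / 73.0 | 78.7 / 77.9 |
| 0.55 | 79.8 / 79.4 | 75.5 / 74.5 | 79.2 / 78.8 |
| 0.60 | 80.2 / 79.3 | 78.2 / 77.0 | 81.1 / 79.5 |
| 0.67 | 79.8 / 79.1 | 81.1 / 80.4 | 83.5 / 82.5 |

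The mean-plus-deviation form beats the single slope in every row, by about 2 to 6 points. Its largest deficit against no baseline is about 1 point (r = 0.50). Type I error was 0.047 to 0.055 throughout.

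**Step 5: other readings of the model sentence.** If all four visits are responses, with every correlation 0.5, power at n = 26 is about 81% (treatment, period and visit terms), 93% (no visit term) or 56% (effect tested as the difference in change from baseline). A paired test on change scores gives 54%: SD = √(64 + 64) = 11.3.

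**The case against.** The protocol's 0.5 is the between-period correlation only. It is nowhere assigned to baseline versus 4 weeks, and the interim paragraph says that value is unknown. If the quoted reliability of 0.67 applied within a period, the shortfall would vanish. **This stands.** A reader might infer that the primary model has about 74% power at the plan's own correlation. The document does not support that, because the figure needs a second correlation that the reviewer supplies. Equally, 0.67 is a general test-retest figure and cannot be taken as the within-period value.

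The model sentence does not say that baseline enters as one covariate, and Step 5 shows readings above and below 80%. **This stands too**, and it means that no single figure can be pinned on the plan.

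The interim re-assessment targets these unknowns. **Largely true.** A reader might infer that it would reuse the paired formula and so miss the problem. That is conjecture: the text says that the baseline-to-follow-up correlation will be used, and the paired formula has no place for it. What is open is only which model's variance it feeds.

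SD 8 is conservative. **Partly.** Take SDs of 7.6 and 5.7 for the two 4-week values, 5.7 for both baselines, every correlation 0.5 and slope 0.44. The adjusted SD is √(7.6² + 5.7² − 7.6 × 5.7 + 0.44² × 5.7²) ≈ 7.3, and power is about 86%. The comparison without baselines gains as well (SD √46.93 = 6.85), so the single slope still costs precision.

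Baseline coding can be left to an analysis plan. Often so, but here the article states both a model and a power, and the two do not correspond.

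**Conclusion.** The point holds as a mismatch between power statement and primary model, not as proof of an underpowered trial. The 80% at 26 patients is correct for a paired comparison of the two 4-week values without baselines. For the mixed model with one baseline slope, the corresponding figure is about 72-74% at a baseline-to-4-week correlation of 0.4-0.5, rising to about 81% at 0.67. That rests on SD 8, all cross-period correlations 0.5, true difference zero, 26 completers and the one-covariate reading. Validity is not in question, since type I error is close to nominal. The point is worth acting on because the model produces the decisive confidence limit, and a form at least as good was available at every correlation examined.

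**What to change.** Three wording changes in the Protocol article's Statistical analysis section, carried into the analysis plan:

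1. **Model.** State that the responses are the 4-week values (T2, T4), with treatment, period and a participant random effect, and that the effect tested is Phe minus placebo at 4 weeks. Enter baseline as two covariates: the patient's mean of T1 and T3, and the period's deviation from that mean.
2. **Power.** Say that the 80% is for the paired comparison without baselines, and give the power of the model actually used over a baseline-to-4-week correlation of 0.4 to 0.67.
3. **Re-assessment.** State that the planned re-assessment, which already draws on both kinds of correlation, will use this same model's variance.

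The cost is one extra coefficient: about 1 point of power at most against no baseline adjustment, if baseline proves uninformative. No additional data or visits are needed.

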The neurotoxicity of Phe during childhood and adolescence is additionally apparent in regard to structural and functional characteristics of the brain [19, 20]. In detail, an estimated 90% of patients with early-treated PKU display periventricular white matter lesions and reduced white matter integrity, which likely impede processing speed, often reported to be reduced in patients with PKU [21, 22]. In contrast, little is known about gray matter changes in PKU. Pérez-Dueñas and colleagues (2006) found volumetric reductions in gray matter structures including the motor cortex and thalamus [23]. However, data were acquired from a mixed sample of early- and late-treated patients, restricting the interpretation of findings. Smaller whole brain volume and smaller parietal and occipital cortex but larger volume of the putamen were described in early-treated patients with PKU [9, 19]. The latter study included patients 9–33 years old, limiting the generalizability of results due to the lack of comparability between the cognitive and neuroimaging data of children and adults. In regard to functional brain networks, atypical brain activation during a working memory task [24, 25] and decreased functional connectivity [10] have been described, likely coming along with cognitive alterations of this vulnerable patient sample. Patients with PKU additionally display neurometabolic alterations in upfield and downfield spectra, such as a decrease in choline concentration [20] and an increase in cerebral Phe level [26], respectively. Due to the limited amount of neuroimaging studies, still much uncertainty exists about the relationship between Phe concentrations and brain abnormalities in adult patients. Importantly, these studies are unable to distinguish between past effects of elevated Phe levels on the brain during childhood and adolescence and a potentially ongoing negative impact in adulthood. Previous intervention studies were mostly open label, associating the level of Phe intake in the diet with cognitive performance [27]. However, the perception of one’s own compliance with dietary recommendations may influence cognitive performance. One small intervention trial investigated the effect of the Phe concentration on cognition in a prospective randomized, placebo-controlled, double-blinded way [28]. Ten Hoedt and colleagues suggested a negative effect of high plasma Phe levels on sustained attention and on mood in nine adult patients with PKU, concluding that “a Phe restricted ‘diet for life’ might be an advisable option for many” [28].

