#### Neuropsychology

Each of the four neuropsychological assessments (T1 to T4) will include evaluations of executive functions, namely working memory (n-back task; Test of Attentional Performance, TAP [37]; Letter-Number-Sequencing; Wechsler Adult Intelligence Scale Fourth Edition, WAIS-IV [38]), inhibition, cognitive flexibility and fluency (Color-Word Interference Test; Delis-Kaplan Executive Function System, D-KEFS [39]). Further, attention (Alertness, Sustained Attention, Divided Attention; TAP [37]), verbal and design fluency (D-KEFS [39]), and fine motor control (Purdue Pegboard [40]) will be assessed.

Psychological questionnaires will be used to assess mood (short form of the Profile of Mood States; POMS [41]), depressive symptoms (Beck’s Depression Inventory; BDI-II [42]) and health-related quality of life (PKU quality of life; PKUQOL [43]). The first neuropsychological assessment will additionally contain the assessment of general intellectual performance (short-form of WAIS-IV [38]).

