### Other outcomes

The PICO Study will further investigate the influence of a 4-week period of Phe load on cognitive performance, specifically on sustained and divided attention, fine motor control, verbal and design fluency, processing speed, mood (short form of the Profile of Mood States, POMS [41]; Beck’s Depression Inventory, BDI-II [42]) and health-related quality of life (PKU quality of life, PKUQOL [43]). Additionally, the influence of temporarily elevated Phe concentrations on integrity of white matter tracts (DTI) and cerebral blood flow (ASL) will be investigated.

Moreover, the study assesses differences between patients with early-treated PKU and healthy controls in regard to cognitive variables, intensity of neural activation during the working memory task, strength of connectivity between brain regions involved in working memory, and structural brain characteristics.

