During the intervention phase, transient mild cognitive impairments might occur due to an increased Phe load. A similar smaller study with increased Phe load over 4 weeks suggested an impairment in sustained attention as well as lower scores in mood profile but did not report any other mild or serious adverse events [28]. Serious side effects are not to be expected. Neither is hyperphenylalaninemia in adulthood known as a cause of metabolic encephalopathy, nor is there a recognized acute decompensation of PKU [51]. The probability of irreversible adverse events during the progress of the present study is therefore extremely low. Even in adult patients with PKU not following any low protein diet for a long time, only very few cases of serious neurologic events with unlikely causal relationship (some of them probably caused by severe vitamin B12 deficiency) have been described in the literature: 11 cases of spastic paraparesis, three cases of muscle weakness/difficulty walking, and three cases of vision loss [52]. Despite not following any low protein diet for a long time, most adult patients showed improved scores for attention as well as self-reported anxiety and depression after reintroducing a low-protein diet [21, 53].

Neuroimaging has become an indispensable tool to better understand brain regions of susceptibility in metabolic disease and to assess the efficacy of dietary treatment on the brain. Clinicians can benefit from the technologic advancements in neuroimaging, allowing for improved understanding of diseases and ameliorated patient management. Only a limited number of neuroimaging studies have been conducted so far in patients with PKU. This is evident on a cross-sectional level but even more so on a longitudinal level. Hence, conclusive evidence on the influence of Phe on brain structure and function is not available with the current state of knowledge. By combining a broad range of advanced MR-techniques, the PICO Study strives to advance our understanding of the disease PKU and its impact on different properties of the brain. The additional information gained by the neuroimaging results may help to characterize subgroups of patients that benefit or do not benefit from restrictive dietary interventions.

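### Mood, a harm suggested by the one earlier blinded trial, is to be described only, with no planned Phe-versus-placebo estimate or interval

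*Protocol article*

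**What the plan says.** The Statistical analysis section of the protocol article settles mood in two sentences: "Simple descriptive statistics will be used for evaluation of questionnaires on adverse events and mood. No formal statistical testing will be performed". The same section applies the linear mixed model (baseline, treatment, period, random participant) to the primary and secondary continuous endpoints. Mood is in neither class.

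The Other outcomes section places mood in the third tier. Its opening sentence, "The PICO Study will further investigate the influence of a 4-week period of Phe load on cognitive performance", goes on to list further outcomes, among them mood, for which it names the short POMS and the BDI-II.

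The article also explains why mood matters. The Background introduces the earlier evidence with "One small intervention trial investigated the effect of the Phe concentration on cognition in a prospective randomized, placebo-controlled, double-blinded way" and reports that this trial "suggested a negative effect of high plasma Phe levels on sustained attention and on mood in nine adult patients with PKU". The Discussion repeats that it "suggested an impairment in sustained attention as well as lower scores in mood profile".

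On collection, the Neuropsychology section says "Each of the four neuropsychological assessments (T1 to T4) will include evaluations of executive functions" and continues "Psychological questionnaires will be used to assess mood (short form of the Profile of Mood States; POMS [41]), depressive symptoms". The one item marked as extra at the first visit is the intelligence test: "The first neuropsychological assessment will additionally contain the assessment of general intellectual performance".

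**The concern.** The aim in Other outcomes is a causal one: what does four weeks of Phe load do to mood, compared with placebo? A randomized crossover answers this with a within-patient treatment difference, adjusted for period, and an interval. Simple descriptive statistics without testing do not commit the trial to either.

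In many trials this would not matter for a third-tier outcome. Here the protocol itself singles out mood as one of two harms suggested by the only earlier blinded trial it describes. Mood is also self-reported, and so particularly exposed to the expectation bias that the Discussion says a blinded design removes. If noninferiority on n-back accuracy is reported, readers will ask what happened to mood. With no planned estimate, any contrast produced later would be post hoc and open to selective reporting.

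**Working it through.** **1. Does another sentence supply the missing estimate?** No. The mixed-model sentence covers primary and secondary continuous endpoints, and mood is listed under Other outcomes. The sentence on mood is specific and points to description. Sustained attention, the other suggested harm, is also an other outcome, but no text restricts it to description.

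**2. Are the data available?** Very probably at T1 to T4. The questionnaires are described within the neuropsychological assessments, and only the intelligence test is marked as additional at the first visit. The grid of Table 1 is not shown, so this is an inference.

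**3. The plan's own sample size.** Inputs from Statistical analysis: SD 8%, between-period correlation 0.5, margin 4%, one-sided alpha 0.05, power 80%.
- SD of the paired difference = √(2 × 8² × (1 − 0.5)) = 8.
- Normal approximation: n = ((1.645 + 0.842) × 8/4)² = 24.7, so 25.
- Noncentral t: power 79.8% at n = 26 and 81.2% at n = 27.

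The stated 26 is reproduced within rounding. The document gives no figure for mood.

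**4. Patients available for mood.** The goal is 30. With the cited dropout of 18% to 30%, 30 × 0.82 = 24.6 and 30 × 0.70 = 21 remain. I use 30, 26 and 21.

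**5. Precision and power for a paired mood difference** (two-sided 5%). Half-width = t(0.975, n − 1)/√n, in SDs of the paired difference; for n = 26, 2.06/5.10 = 0.404. Power is from the noncentral t with noncentrality δ√n, where δ is the true effect in the same units.

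| n | 95% CI half-width | Effect detectable with 80% power | Power at 0.3 SD | Power at 0.5 SD | Power at 0.8 SD |
|---|---|---|---|---|---|
| 30 | 0.37 | 0.53 | 36% | 75% | 99% |
| 26 | 0.40 | 0.57 | 31% | 69% | 98% |
| 21 | 0.46 | 0.64 | 26% | 59% | 94% |

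With nine patients, as in the earlier trial, power at 0.5 SD would be 26%.

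**6. Conversion to the SD of the score itself.** Multiply by √(2(1 − r)), where r is the between-period correlation. The documents give no r for POMS or BDI-II, so I assume 0.3 to 0.67. At n = 26 the half-width is then 0.48 (r = 0.3), 0.40 (r = 0.5) or 0.33 (r = 0.67) raw SD.

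These are paired-t approximations. The period term costs a degree of freedom, and baseline adjustment may gain some precision.

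**The case against.** The strongest defence is that describing a third-tier outcome in a 30-patient trial is a recognised and cautious choice that keeps unplanned significance claims down. That stands, and it is why this is not an error. Studying an influence does not promise a hypothesis test, so the Other outcomes and Statistical analysis sections do not strictly contradict each other.

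A reader might infer that the plan forbids any inference on mood, or that it will summarise mood visit by visit and discard the pairing. The text says neither. It excludes formal testing. A table of within-patient differences, or an interval without a test, would be compatible with it, and table layout is commonly left to the analysis plan, which is not shown. What remains is that the article commits to neither.

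A reader might also infer that an interval of ±0.40 SD would show or exclude a moderate mood effect. It would not do so reliably. At n = 26 the chance of showing a true 0.5 SD effect is 69%. If the true effect is zero, the chance that the interval excludes a 0.5 SD harm is, by symmetry, the same. At n = 21 both are 59%. The limited precision supports modest labelling. It does not support leaving the estimate out, because an interval shows that uncertainty and a descriptive table need not.

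Finally, the reach of the sentence on mood is not fully clear. Neuropsychology separates mood (POMS) from depressive symptoms (BDI-II), whereas Other outcomes groups both under mood. The BDI-II is outside the mixed-model sentence on either reading.

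**Conclusion.** The point holds as a suboptimal analysis choice. The protocol sets out to study the effect of Phe load on mood and names mood as a harm suggested by the one earlier blinded trial. It then commits to no period-adjusted Phe-versus-placebo estimate or interval. No figure in the document is wrong, and the primary analysis is unaffected.

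The data could support an exploratory estimate that is informative about large effects, has roughly 59% to 75% power at 0.5 SD of the paired difference, and cannot exclude small effects. This assumes 21 to 30 analysable patients, approximately normal paired differences and collection at all four visits. The meaning in POMS or BDI-II points is unknown, because the documents give no SD for either scale.

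It would be too strong to infer that the trial will be used on its own to justify relaxing the diet while mood goes unexamined. The Discussion frames the dietary question broadly, but it says that noninferiority could justify a larger long-term trial and names the simulated diet and short duration as limitations. Mood will still be collected and summarised.

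**What to change.** In the Statistical analysis section, separate the two kinds of questionnaire:

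- **Adverse events:** keep simple descriptive statistics.
- **POMS and BDI-II:** fit the mixed model already specified for the primary and secondary endpoints (baseline, treatment and period as fixed effects, participant as random effect). Report the Phe-minus-placebo difference with a two-sided 95% confidence interval, labelled exploratory and without a confirmatory test. Name both instruments, so that it is clear the BDI-II is covered.

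This needs no new data, visits or patients, and spends no alpha. It takes two model fits, or slightly more if POMS subscales are reported separately. The downside is a few additional exploratory estimates without multiplicity control, which the label should make plain.
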